Alternative treatment such as acupuncture has been recognized with the efficacy and safety in treating insomnia [17]. A clinical trial has suggested electroacupuncture (EA) significantly improves the quality of sleep in patients with depression [18]. Moreover, acupuncture promotes renal function, reduces proteinuria, controls hypertension, corrects anemia, relieves pain, and controls many hemodialysis-related complications including insomnia in patients with CKD [19,20]. However, there is no clinical trial demonstrating the efficacy and safety of EA in treating insomnia in ESRD undergoing MHD, and a sham-controlled trial is considered by the systematic review to have a low risk of bias in all areas, including selection, conduct, detection, attrition and reporting [21]. Therefore, our study aims to investigate the efficacy and safety of EA in relieving insomnia in ESRD undergoing MHD using a randomized, sham-controlled clinical trial. We present this article in accordance with the SPIRIT reporting checklist.

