### Participants

2.2.

Participants will be recruited from the hemodialysis department of Beijing Dongcheng First People’s Hospital. The enrolment began in June 2023 and is anticipated to be completed by June 2024. Each eligible and consented patient will be randomly assigned in a 1:1 ratio to receive 4-week EA or sham EA.

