#### Sham group

2.5.2.

Twenty non-acupoints based on literature review [28,29] and the clinical practice will be used in sham group (locations are shown in Table 2 and Figure 4). Participants will use an opaque patch to cover their eyes and lie in a prone position, acupuncturists will use 75% alcohol pads to sterilize the skin around the acupoints and then insert disposable needles into the acupoints. Needles will be inserted at an angle of 90° and a depth of 2–3 mm (superficial penetration) in acupoints located in face and will be inserted at an angle of 90° and a depth of 2–3 mm in acupoints located in limbs and abdomen without any manipulation like lifting and thrusting or twirling and rotating to avoid De qi sensation. The sham electrodes from the EA apparatus will be connected to the needle handles at non-acupoint 1 (NA1) and NA2. The sham electrode lines will be identical to the real one, but the inner metal wires will be cut off. Therefore, no current will be outputted with the EA apparatus in a power-on state with a lighted power indicator and voice of clatter. The parameters of sham EA apparatus and treatment will be the same as in the EA group. Participants will be treated individually to avoid communication.

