### Sample size

2.7.

No previous study has been found to use the response rate to evaluate EA for insomnia in end-stage renal disease undergoing MHD. A formal sample size calculation is not necessary in our exploratory study. Thus, recruitment will take place for a participant sample size of 60, with 30 individuals per group, to obtain the practical aim of our study based on clinical experience [36].

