### Statistical analysis

2.8.

A biostatistician, who is blinded to the data, is accountable for conducting statistical analyses employing SAS (SAS Institute located in Cary, NC, USA) and R software (version 4.2.1). Intention-to-treat (ITT) is our statistical strategy that includes all participants who have been randomized and received at least one intervention session. Demographic characteristics will be summarized for each group. Mean (standard deviation) or median (interquartile range) will be used to describe continuous variables depending on distribution’s normality. Percentage will be used to describe categorical variables. Regarding primary outcomes, a Chi-squared test will be applied to compare the response rate between treatment group and control group. For secondary outcomes, continuous variables including sleep diary, ISI, PSQI, SF-12, FSS, ambulatory blood pressure, and plasma levels of CRP and D-Dimer will be analyzed according to repeated measurement using a mixed-effects model. α will be set at 0.025 for the primary outcome, and it will be set at 0.05 for multiple comparisons of the secondary outcomes. Besides, the 95% confidence interval (95% CI) will be used to assess effect size of primary and secondary outcomes. A Chi-squared test will be applied for the compliance scores and adverse events rate. Last observation carried forward method will be used for the dropout analysis. Sensitivity analysis will be conducted using per-protocol (PP) analysis, which consists of all participants who meet all eligibility criteria and are randomized, complete the treatment and follow-up plan, without any major protocol deviations.

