We cautiously designed the present study according to relevant guidelines, the study adheres to well-established methodological requirements, including adequate randomization, allocation concealment, and blinding of participants, outcome assessors and statisticians, providing reliable evidence on the efficacy and safety of EA for insomnia in ESRD undergoing MHD. Specifically, we will evaluate beneficial effects of EA on sleep onset latency, wake after sleep onset, early morning awakening, total wake time, total sleep time, and sleep efficiency. We will use computer-produced randomization and allocation concealment from a third party to minimize selection bias and apply block randomization to ensure a balanced prognosis between intervention groups. Participants, data analysts, and outcome assessors will be blinded to group allocation. The allocation of all participants will be concealed until the statistical analysis is completed. All processes follow traditional Chinese medicine theory and clinical practice. Due to the increased nocturnal systolic BPV and inflammatory factors induced by insomnia in ESRD patients, we will adopt outcome measurements including 24-Hour ambulatory blood pressure and blood sample (plasma levels of C-reactive protein (CRP) and D-Dimer) to objectively investigate the effect of EA for insomnia in ESRD undergoing MHD. There will be 3 sessions each week during the 4-week treatment period, resulting in a total of 12 sessions with a 4-week follow up. The well-designed study can provide a profound impact on the clinical practice of EA for insomnia in ESRD undergoing MHD.

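### Safety is a stated aim, but its only inferential analysis is a chi-squared test against a skin-penetrating sham at 30 per arm, with no interval specified for adverse events

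*Protocol article*

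**What the plan says.** The Introduction states the purpose: "our study aims to investigate the efficacy and safety of EA in relieving insomnia in ESRD undergoing MHD". The closing paragraph of the Discussion repeats it. Earlier in the Discussion the design is described as "providing reliable evidence on the efficacy and safety of EA for insomnia in ESRD undergoing MHD".

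Section 2.8 gives the safety analysis in one sentence: "A Chi-squared test will be applied for the compliance scores and adverse events rate". The same section says that "the 95% confidence interval (95% CI) will be used to assess effect size of primary and secondary outcomes". Section 2.6.2 lists the secondary outcomes and adverse events are not among them; they have their own section, 2.6.4, which names post-needling pain, dizziness, hematoma and infection as common event types. Section 2.8 also says that categorical variables will be described by percentages. No adverse event rate, margin or significance level for adverse events is given.

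On size, section 2.7 says "recruitment will take place for a participant sample size of 60, with 30 individuals per group" and "A formal sample size calculation is not necessary in our exploratory study". On the comparator, section 2.5.2 describes twenty sham sites: "Needles will be inserted at an angle of 90° and a depth of 2–3 mm (superficial penetration"), with the same depth for limbs and abdomen, no manipulation and no current. Section 2.5 states that every participant receives heparin as part of dialysis.

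**The concern.** A safety claim is supported by showing how large the harm could still be. A test of equality does not show that, and in a small sample it will usually be non-significant whether or not there is harm. Here the article fixes such a test for adverse events and attaches intervals to the other outcomes.

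The comparator adds a separate difficulty. Both arms have skin punctured at 20 sites in heparin-treated patients, so pain, hematoma and infection can occur in both. Whatever risk the arms share cancels from a between-arm test. More patients would not cure this, because the test addresses the excess over sham needling, whereas a clinician considering EA also needs its absolute risk.

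At stake is how a result such as 9/30 v 3/30 is reported. The percentages would appear as 30% and 10%, accompanied by a non-significant p-value and nothing to show how large an excess the data allow.

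**Working it through.** **Inputs from the protocol article.** 30 per arm, 1:1 (sections 2.2 and 2.7); chi-squared test of the adverse event rate (2.8). The 60 patients do not come from a calculation, so there is no power figure to reproduce.

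**Assumptions.** Two-sided alpha 0.05, since none is stated for adverse events; uncorrected Pearson test, since no correction is mentioned; all event rates, since the article gives none.

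**1. Rejection rule.** With a events in EA, b in sham, n = 30 and t = a + b, the statistic is χ² = 2n(a − b)² / [t(2n − t)], and the test rejects above 3.84. Some values:

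- 3 v 0: 60 × 9 / (3 × 57) = 3.16, not significant.
- 4 v 0: 60 × 16 / (4 × 56) = 4.29, significant.
- 9 v 3: 60 × 36 / (12 × 48) = 3.75, p = 0.053, not significant.
- 10 v 3: 60 × 49 / (13 × 47) = 4.81, significant.

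For 9 v 3 the Newcombe 95% CI for the risk difference runs from −0.5 to +39 percentage points.

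**2. Chance of missing a true excess.** This is 1 minus the sum, over all 31 × 31 tables that reject, of Bin(a; 30, p_EA) × Bin(b; 30, p_sham).

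| Sham v EA (assumed) | Pearson, 0.05 | Yates or Fisher, 0.05 | Pearson, 0.025 |
|---|---|---|---|
| 10 v 40% | 20% | 30% | 29% |
| 10 v 30% | 50% | 63% | 61% |
| 5 v 15% | 74% | 91% | 84% |
| 20 v 30% | 86% | 91% | 91% |
| 1 v 5% | 95% | 99.8% | 99% |

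For 80% power the required numbers per arm are 62 (10 v 30%), 141 (5 v 15%) and 199 (10 v 20%). With fewer than 10 affected participants in total, the expected event count per arm is below 5. The uncorrected approximation is then doubtful, and Yates or Fisher, as the table shows, misses more.

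**3. What intervals would show.** The exact two-sided 95% upper limit for 0/30 is 1 − 0.025^(1/30) = 11.6%. For 1, 2 and 3 events in 30 the Clopper-Pearson upper limits are 17.2%, 22.1% and 26.5%. Newcombe 95% CIs for EA minus sham, in percentage points, are:

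- 0 v 0: −11.4 to +11.4
- 3 v 3: −16.9 to +16.9
- 6 v 3: −8.8 to +28.5

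All three results are non-significant, yet they are compatible with excesses of about 11 to 29 points.

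**4. Comparator.** The EA points in section 2.5.1 add up to 20 needles, the same number as in the sham. Depth differs: 5–10 mm on the scalp and 20–30 mm elsewhere, with manipulation and scalp current, against 2–3 mm with neither. So part of the needling risk is shared and cancels from the test, and part is not.

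**The case against.** Four counter-arguments deserve weight.

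- **Percentages will be shown.** Section 2.8 promises percentages for categorical variables, so a tripling of events would be visible and a reader could compute an interval from 30 per arm. This stands, and it rules out saying that the plan offers nothing but a p-value. The percentages still carry no uncertainty, and the only inference the authors commit to is the test.
- **No decision rule is written.** A reader might infer that a non-significant test will be taken as proof of safety. The article does not say so. Its phrase about reliable evidence is general Discussion wording, linked to randomization, concealment and blinding. That stronger reading is not supported; the point concerns which analysis was chosen.
- **It is a pilot with disclosed low power.** Section 2.7 calls the study exploratory, and the Discussion concedes that the small sample may lower power. That answers a complaint about sample size. It does not make a test preferable to estimation, and it does not touch the shared-risk issue.
- **Safety detail may sit in a document not shown.** Event tables often do, and the interval sentence does not say that other outcomes are excluded. So the absence of an interval would not be a finding by itself. What can be criticised is the analysis that the article does state.

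A reader might also infer that the sham hides all needling risk, or that one miss rate describes this trial. Neither holds. EA needling is deeper, manipulated and electrified, so only part of the risk is common to both arms. The miss rates depend wholly on the assumed event rates. Patients with hemorrhagic disease are also excluded (section 2.2.3), which tempers the bleeding argument.

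**Conclusion.** The point holds in this form: for a stated aim, the article chooses a test of equality as its sole inferential safety analysis, against a comparator that shares part of the risk, and specifies intervals only for outcomes that exclude adverse events. At 30 per arm the miss rate runs from about 20% to 95% over the scenarios considered. These rest on assumed event rates, an assumed alpha of 0.05 and the uncorrected test. The 11.6% upper limit for 0/30 needs no assumed event rate. This is a change worth making before analysis; it is not a flaw that invalidates the trial.

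**What to change.** In section 2.8, replace the chi-squared test as the basis for safety:

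- For each arm, report the number and proportion of participants with any adverse event, with each event type in section 2.6.4 and with a serious adverse event, each with an exact (Clopper-Pearson) 95% CI.
- Report the EA minus sham risk difference with a Newcombe 95% CI.
- Base the safety statement on these estimates and their upper limits, including the EA arm's own rate, because the sham also penetrates the skin.
- Keep the chi-squared p-value as descriptive only, and state that a non-significant difference is not evidence of safety.

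The cost is a sentence or two and one extra table from data already being collected. The drawback is a less favourable safety statement, because the intervals will be wide at this sample size.

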#### Secondary outcome measurement

2.6.2.

Sleep diary: Participants will be required to complete a daily sleep diary during the whole trial, the variables in the daily sleep diary include sleep onset latency, wake after sleep onset, early morning awakening, total wake time, total sleep time, and sleep efficiency [31].Insomnia Severity Index (ISI): ISI will also be used as one of the secondary outcomes, details of ISI are presented in primary outcome measurement section [31,32]. ISI will be applied at baseline, Week 4 and 8Pittsburgh Sleep Quality Index (PSQI): PSQI will be used to assess sleep quality and disturbances over the past month. PSQI is composed of 19 items including 4 open questions, and 15 Likert-type questions that score for each question ranging from 0 to 3. Individual item scores yield 7 components. The final score is acquired by adding the 7 component scores. Higher scores indicate more acute sleep disturbances, and a cut-off score of 5 suggests poor sleep quality [33]. PSQI will be applied at baseline, Week 4 and 8.Short Form Health Survey-12 (SF-12): SF-12 will be used to detect the quality of life. The SF-12 comprises both mental and physical components, with each part ranging between 0 and 100. Higher scores indicate a greater quality of life [34]. SF-12 will be applied at baseline, Week 4, and 8.Fatigue Severity Scale (FSS): FSS is a 9-item questionnaire and will be used to assess the severity of fatigue and how it affects certain activities. Each item is scored on a seven-point scale, the total score ranges from 9 to 63. Higher scores indicate more severe fatigue [35]. FSS will be applied at baseline, Week 4, and 8.(6) 24-Hour ambulatory blood pressure: 24-Hour ambulatory blood pressure monitoring will be applied as baseline, Week 4, and 8 to evaluate the night blood pressure, the results will be interpreted by a specific cardiovascular specialist.Blood sample: Blood samples will be collected at baseline, Week 4, and 8 to compare the levels of C-reactive protein (CRP) and D-Dimer.

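### Carrying the last observation forward before the mixed models adds avoidable bias to the visit-based secondary outcomes; for the primary outcome it is an undeclared non-responder rule with only a weak check

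*Protocol article*

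**What the plan says.** Section 2.8 of the protocol article fixes one rule for participants who leave: "Last observation carried forward method will be used for the dropout analysis". It does not say which outcomes the rule covers; the natural reading is all of them.

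The same section compares response rates (a fall of at least 7 ISI points at Week 4) with a chi-squared test at α = 0.025. It says that the continuous secondary outcomes "will be analyzed according to repeated measurement using a mixed-effects model". The only robustness check is this: "Sensitivity analysis will be conducted using per-protocol (PP) analysis". That set is limited to participants who complete treatment and follow-up without major deviations.

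Section 2.6.2 sets the measurement times. For the questionnaires: "ISI will be applied at baseline, Week 4" and again at Week 8; "PSQI will be applied at baseline, Week 4 and 8"; "SF-12 will be applied at baseline, Week 4, and 8"; "FSS will be applied at baseline, Week 4, and 8". For CRP and D-Dimer: "Blood samples will be collected at baseline, Week 4, and 8". Ambulatory blood pressure follows the same three visits. The sleep diary is the exception: it is kept daily throughout the trial.

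**The concern.** With one measurement at the end of treatment and one at follow-up, there is little to carry forward. A participant lost before Week 4 gets the baseline value, so change is zero at both later visits. A participant lost between Weeks 4 and 8 gets a Week 8 value copied from Week 4, as if the effect neither faded nor grew. For the diary, the last daily entry is carried instead.

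A likelihood-based mixed model does not need these values. It uses whatever visits a participant has and is valid under missing at random. Filling the gaps first gives up that property and treats copies as measurements.

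At stake are the size of the Week 4 secondary effects, the meaning of Week 8, which is the only follow-up visit, and, if the arms lose different numbers, the direction of the error. The per-protocol analysis leaves the dropouts out, so it says little about how their missing values should be handled.

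**Working it through.** The article gives no dropout rate, standard deviation or effect size, so there is no planned figure to reproduce. Only the 30 per arm, the visit schedule, the 7-point response rule and the tests come from the document. All other inputs below are assumptions.

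**1. Secondary outcomes, no true effect.** Suppose both arms improve by 5 ISI points and fractions d₁ (EA) and d₀ (sham) leave before Week 4, unrelated to outcome. Carrying baseline forward makes the expected improvement 5(1 − d), so the false difference is 5 × |d₁ − d₀|.

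- 20% against 5%: 5 × 0.15 = 0.75 points, against whichever arm loses more.
- Equal loss: 5 × 0 = 0.

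**2. Secondary outcomes in the planned type of model.** Simulation: 30 per arm, three visits, 1,500 replicates, REML mixed model (visit by arm, compound symmetry), SD 4.5, correlation 0.5. Dropout is completely at random, half before Week 4 and half between Weeks 4 and 8. Entries are EA minus sham in change from baseline, Week 4 / Week 8.

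| Loss EA / sham | True | Observed data, no imputation | Carried forward |
|---|---|---|---|
| 20% / 20% | −3 / −2 | −3.01 / −2.03 | −2.74 / −1.95 |
| 30% / 10% | −3 / −2 | −3.02 / −2.00 | −2.18 / −1.65 |
| 30% / 10% | 0 / 0 | −0.02 / 0.03 | 0.47 / 0.31 |
| 20% / 20%, effect gone by Week 8 | −3 / 0 | −2.99 / 0.06 | −2.68 / −0.23 |

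These can be checked by hand. In row 1, 10% of each arm is lost before Week 4, so the Week 4 difference is 0.9 × (−3) = −2.70. In row 2, EA improves 7 and sham 4 points at Week 4, with 15% and 5% lost by then: −7 × 0.85 + 4 × 0.95 = −5.95 + 3.80 = −2.15. In row 4, both arms are 3 points better than baseline at Week 8, but the 10% lost after Week 4 keep their Week 4 improvements of 7 and 4. EA: −(0.1 × 7 + 0.8 × 3) = −3.1. Sham: −(0.1 × 4 + 0.8 × 3) = −2.8. The difference is −0.30 where the truth is 0; the simulated −0.23 agrees within simulation error.

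In the null row, a nominal 5% test rejected 7.6% of the time at Week 4 and 6.1% at Week 8 under carrying forward, against 5.2% and 5.5% on observed data.

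**3. Precision.** In row 1 the carried-forward model reported a standard error of 1.13 at both visits, against empirical standard deviations of 1.17 and 1.14. In row 2 it reported 1.14 against 1.19 and 1.18. The understatement is at most about 4% (1.14 / 1.19 = 0.96).

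**4. Primary outcome.** A participant lost before Week 4 has zero change and so is a non-responder. With true rates p₁, p₀ and loss unrelated to outcome, the expected difference is p₁(1 − d₁) − p₀(1 − d₀). For 50% against 30%, a true difference of 20 points:

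- 10% / 10%: 0.50 × 0.90 − 0.30 × 0.90 = 0.18
- 20% / 10%: 0.50 × 0.80 − 0.30 × 0.90 = 0.13
- 10% / 20%: 0.50 × 0.90 − 0.30 × 0.80 = 0.21

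With equal true rates of 40%, loss of 20% against 5% gives 0.40 × (0.95 − 0.80) = 0.06, a false 6-point difference.

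**The case against.** The strongest defence concerns the primary outcome. A chi-squared test on a binary response needs some rule for a missing Week 4 score, and counting dropouts as non-responders is common and defensible. Equal loss then shrinks the difference without inflating false positives. This stands: the remaining gap is that the rule is not declared as non-response and has only a weak check. Replacing it with multiple imputation as the main analysis, at 30 per arm, would be a matter of preference.

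It can also be said that this is an exploratory pilot and that with negligible dropout nothing happens. Both are true. But the article states the method outright, so it is not a detail left to an unseen plan, and with 30 per arm six losses are already 20% of an arm.

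A reader might infer more than the documents support:

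- **That every early dropout reverts to baseline on every outcome.** The daily diary carries its last entry.
- **That standard errors are clearly too small.** Take change with mean 5 and SD 5, 30 per arm, and 20% set to zero. The standard error is then about 0.89, against about 1.01 on observed data. But the variance of the filled-in values is 0.8 × (25 + 25) − 4² = 24, and √(24/30) = 0.894 is also the true sampling SD of that mean. The gap compares two different estimators; it does not show false precision.
- **That the false-positive rate nearly doubles.** A simulated 9.2% needs 20% against 5% loss, all before Week 4, in a two-sample test at 5% that the plan does not use. The same setup gave 5.5% at 10% against 5%, and 4.8–5.1% with equal loss. For the planned chi-squared test at 0.025, with equal true response of 30–50%, the rate was about 2.7–3.0% at 10% against 5% loss and 3.8–5.4% at 20% against 5%.
- **That the per-protocol analysis is no check at all.** A divergence from the main result would be some signal, though one mixed with the effect of removing protocol deviators.

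**Conclusion.** The point holds for the secondary outcomes measured only at the three visits. Carrying values forward before a model that can use incomplete records adds bias for no gain. Under equal loss it attenuates the Week 4 effect; under unequal loss it can push in either direction; and it makes the Week 8 result partly a copy of Week 4.

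The size rests wholly on assumed dropout. It is about 0.75 ISI points with no true effect, 5 points of improvement in both arms and 20% against 5% early loss, and zero there with equal loss. In the mixed-model example with 30% against 10% loss, a true −3.0 at Week 4 becomes about −2.2. These figures take dropout as unrelated to outcome; the observed-data model is itself only as good as missing at random. Any understatement of standard errors is modest.

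For the primary outcome the implied rule is acceptable, but it should be named and tested, because unequal loss moves a true 20-point difference to 13 or 21 points in the examples. This should be fixed; it does not invalidate the trial.

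**What to change.** In section 2.8:

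- Delete last observation carried forward for the secondary outcomes, and state that the mixed models are fitted to all observed data without imputation.
- For the primary outcome, state that a missing Week 4 ISI counts as non-response.
- Add one sensitivity analysis for the primary: multiple imputation of the Week 4 ISI score from baseline ISI, arm and diary data, with response derived afterwards.
- Keep the per-protocol analysis as supplementary, not as the check on missing data.

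The cost is revised wording, a little programming and slightly wider intervals for the secondary outcomes (in the 20% per arm example, standard errors of 1.21 and 1.26 instead of 1.13). No new data are needed. The change should be recorded before allocation is revealed, so that the choice cannot appear to depend on the results.

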**Methods:**

This is a study protocol for a pilot randomized, sham-controlled, single-center, clinical trial. A total of 60 patients with insomnia in ESRD undergoing MHD will be randomly assigned to treatment group (EA, 3 sessions per week for 4 weeks), or sham group (sham EA, 3 sessions per week for 4 weeks) in a 1:1 ratio. Participants will complete the trial by visiting the research center at Week 8 for a follow-up assessment. The primary outcome is the response rate: the proportion of patients achieving a minimal clinically important difference, which is defined as ≥7 points on insomnia severity index (ISI) at Week 4 compared with baseline. Secondary outcomes include sleep diary, ISI, pittsburgh sleep quality index (PSQI), short form health survey-12 (SF-12), fatigue severity scale (FSS), 24-Hour ambulatory blood pressure, and plasma levels of C-reactive protein (CRP) and D-Dimer.

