### Study design and setting

2.1.

This study proposes a single-center, sham-controlled, randomized controlled trial (RCT) at Beijing Dongcheng First People’s Hospital. The study was approved by the research ethic committee. The study will undergo quarterly audits by the Ethics Committee to determine if early termination is necessary. This study will be conducted following the Declaration of Helsinki (as revised in 2013). Written informed consent will be obtained from all participants. Recruitment strategies include posting online advertisement *via* the hospital website and Chinese social media (WeChat), as well as flyers at outpatient unit [22,23]. The intervention includes 4 weeks of EA or sham EA and 4 weeks of follow-up (Figures 1 and 2).

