#### Primary outcome measurement

2.6.1.

The primary is the response rate, which reflects the proportion of participants whose average Insomnia Severity Index (ISI) scores decrease by at least 7 units [30,31] at Week 4 compared with baseline. The ISI is a 7-item self-administrated instrument to evaluate the nature, severity, and impact of insomnia during daytime and nighttime. A 5-point Likert scale is used to score each item, consisting of a total score ranging from 0 to 28: where 0–7 = No clinically significant insomnia, 8–14 = Subthreshold insomnia, 15–21 = Clinical insomnia (moderate severity), 22–28 = Clinical insomnia (severe) [31,32]. The minimal clinically important difference (MCID) of ISI is 7 units [30,31].

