#### Compliance assessment

2.6.3.

Participants who achieve scores above 80 will meet the criteria for good compliance by the end of Week 4.

$$\text{Compliance score}=\frac{\text{Acutual treatment sessions}}{\text{Required treatment sessions}}x100$$

E.g. a participant undergoes 6 treatment sessions, as 12 sessions are required in this study, based on the equation, the compliance score amounts to 50, denoting inadequate compliance.

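### The only per-protocol set requires completed follow-up to Week 8, so it can drop valid Week 4 primary outcomes because of a later missed visit (minor)

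*Protocol article*

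**What the plan says.** The primary outcome (section 2.6.1) is the proportion of participants whose ISI "scores decrease by at least 7 units [30,31] at Week 4 compared with baseline". Section 2.1 sets the timeline: "The intervention includes 4 weeks of EA or sham EA and 4 weeks of follow-up". The Methods paragraph of the abstract places the end of follow-up: "Participants will complete the trial by visiting the research center at Week 8 for a follow-up assessment". Follow-up therefore means the four weeks after the primary endpoint.

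Section 2.8 gives two analysis sets. The main one, labelled intention-to-treat, "includes all participants who have been randomized and received at least one intervention session". The other is the only sensitivity analysis named: "Sensitivity analysis will be conducted using per-protocol (PP) analysis". Its members must meet the eligibility criteria, be randomised, and "complete the treatment and follow-up plan, without any major protocol deviations". The article describes this one set for all outcomes and gives no version specific to Week 4.

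**The concern.** The per-protocol definition has two separate parts: completing treatment and follow-up, and having no major deviation. The word *major* limits the second part only. Completing follow-up is a membership condition in its own right, and follow-up ends at Week 8.

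Consider a participant who finishes treatment, completes the ISI at Week 4 and does not return at Week 8. The primary outcome is known and nothing about it is in doubt. The main analysis keeps this person, but the per-protocol analysis of the same outcome does not.

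Two things are at stake. First, attendance at Week 8 comes after the outcome and may depend on it, for example if people who did not improve have less reason to come back. Selecting on it can shift the Week 4 comparison in a way that selection on events up to Week 4 would not. Second, observed outcomes are discarded in a trial with 30 participants per arm.

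**Working it through.** **What can be reproduced.** The article gives no response rates, no dropout rate and no formal sample size calculation, so there is no planned figure to reproduce. The check is a comparison of time points, followed by illustrations.

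**Time points**

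| Element | Time point | Place |
|---|---|---|
| Treatment ends | Week 4 | 2.1 |
| Primary outcome | Week 4 | 2.6.1 |
| Follow-up ends | Week 8 | 2.1; abstract, Methods |
| Per-protocol membership settled | after completed follow-up, so Week 8 | 2.8 |

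Membership is settled four weeks after the outcome that the set is used to check.

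**Inputs for the illustrations.** From the protocol: 30 per arm (section 2.7) and 95% confidence intervals (section 2.8). Assumed: all response rates and all losses between Week 4 and Week 8.

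**Precision under random loss.** Assume 50% response with EA and 30% with sham. The Wald half-width is 1.96 × √[0.5 × 0.5/n + 0.3 × 0.7/n] = 1.96 × √(0.46/n).

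- No loss, n = 30: 1.96 × √(0.46/30) = 24.3 points
- 10% loss, n = 27: 1.96 × √(0.46/27) = 25.6 points
- 20% loss, n = 24: 1.96 × √(0.46/24) = 27.1 points

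The interval widens by 1.3 to 2.8 points on each side.

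**Bias when loss depends on the Week 4 result.** Suppose Week 4 shows 15/30 vs 9/30, a difference of 50.0% − 30.0% = 20.0 points. Only non-responders miss Week 8.

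- 1 EA and 6 sham non-responders lost: 15/29 − 9/24 = 51.7% − 37.5% = 14.2 points
- 6 EA and 1 sham non-responders lost: 15/24 − 9/29 = 62.5% − 31.0% = 31.5 points

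**A milder pattern.** Assume true rates of 60% vs 30% (30 points). In one group of non-responders 20% miss Week 8; everyone else has 5% loss. The retained response rate is p(1 − loss in responders) / [p(1 − loss in responders) + (1 − p)(1 − loss in non-responders)].

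- EA non-responders lost more: 0.6 × 0.95 / (0.6 × 0.95 + 0.4 × 0.80) = 64.0%; sham stays at 30.0%; difference 34.0 points
- Sham non-responders lost more: 0.3 × 0.95 / (0.3 × 0.95 + 0.7 × 0.80) = 33.7%; EA stays at 60.0%; difference 26.3 points
- Non-responders lost more in both arms: 64.0% − 33.7% = 30.3 points

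The estimate can move either way. In the third case, where the dependence on response is the same in both arms, it hardly moves.

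**The case against.** The strongest reply is that this is a sensitivity analysis. The primary result comes from the set of treated randomised participants and is untouched. Any per-protocol set selects on events after randomisation, so some selection bias comes with the method. A single completer set across outcomes is common, and here it also serves Week 8 secondary outcomes, for which completed follow-up is relevant. The article is condensed, and a fuller document may define sets by visit. Heavy loss is also not obvious, since participants dialyse three times a week and are recruited from the hospital's own hemodialysis department. All of this stands, and it is why the point is minor. It does not remove the point: the follow-up condition is stated, not merely left undefined, and its relevance to Week 8 is no reason to apply it to a Week 4 outcome.

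A reader might infer three stronger claims. The documents do not support them.

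- *That section 2.8 contradicts the compliance rule.* Section 2.6.3 says "Participants who achieve scores above 80 will meet the criteria for good compliance by the end of Week 4", which means at least 10 of 12 sessions (10/12 = 83.3; 9/12 = 75.0). Section 2.8 does not say that completed treatment means 12 of 12, and it does not tie the per-protocol set to this score. The link is undefined, which is detail that a fuller document may supply. It is not a contradiction. Requiring completed treatment is the ordinary purpose of such a set.
- *That participants are removed for trivial reasons.* Only major deviations exclude, and nothing says that one missed session does.
- *That the analysis cannot serve as a check on the Week 4 result.* It is a weakened check. Agreement or disagreement with the main analysis remains informative.

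**Conclusion.** The point holds in a limited form. Followed as written, section 2.8 removes observed Week 4 outcomes from the only named sensitivity analysis of the primary outcome because of an event after the endpoint.

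Under the assumed 50% vs 30% response and random loss, the precision cost is small for a pilot trial. The bias could be larger: under the assumed lopsided losses a 20.0-point difference becomes 14.2 or 31.5 points, and under the milder pattern 30 points becomes 26.3 or 34.0. Every loss and response rate here is an assumption, and the 6-versus-1 split is a deliberately strong one. The documents give no basis for predicting the direction of the bias, or that it will occur at all. The main analysis is unaffected. Severity: minor.

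**What to change.** Define the per-protocol set for the primary outcome as participants who are eligible, randomised, completed treatment, have a Week 4 ISI, and have no major deviation up to Week 4. Require Week 8 completion only in the set used for Week 8 outcomes. The compliance score above 80 in section 2.6.3 could serve as the treatment-completion criterion, but the documents do not oblige it. The wording should be settled before the allocation is revealed to the analysts.

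The cost is about one sentence and no new data. The downside is one extra set definition, and two per-protocol sets of different size to report. The revised set still selects on events after randomisation, as any per-protocol set does, but no longer on events after the primary endpoint.
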